#### Treatment Arm 1: MFG-HIVSR Plus FEE

In addition to the bolstered usual care described earlier, adolescents living with HIV and their caregivers will participate in a family strengthening intervention delivered via MFG along with an FEE component. MFG is a family-centered, group-delivered, evidence-informed, strength-based 10-session (weekly) intervention for children whose families struggle with poverty and associated stressors. It integrates components of existing evidence-based practices that successfully improve parental management, mental health–promoting family processes, and family strengthening [77,104,105,121,131-134]. For the purpose of M-Suubi, MFG-HIVSR has 6 additional sessions to cover HIV stigma–related issues. The specific MFG-HIVSR session content will be based on our previous interventions [79,103-105,121,132,133,135-145]. Sessions will focus on the core MFG components, also known as 4 Rs and 2 Ss (rules, responsibility, relationships, respectful communication, stress, and social support). Sessions focused on HIV stigma will be adapted from the existing Suubi curriculum and resources from the Ministry of Health. Each session provides opportunities to contextualize the content to the realities of family life and emergent cultural and values perspectives and tailor messages to the child’s age. These will include group activities, role-plays, sharing experiences, and family take-home activities. Families (adolescents living with HIV and their caregivers) will be combined into groups of up to 10 families to promote communication and support within and among families. MFG-HIVSR sessions will last approximately 1 hour and will be delivered twice weekly during school holidays when adolescents living with HIV are more readily available. Parent peer and community health workers already trained in MFG delivery will be recruited and will receive refresher training on M-Suubi’s content on HIV stigma. During MFG-HIVSR implementation, facilitators will receive 2 hours of monthly group supervision across sites. Given the significant and protective role families play in the health and well-being of adolescents living with HIV, we expect that strengthening family functioning and dialogue by involving caregivers through MFG-HIVSR will lead to better child outcomes, including reduced HIV stigma. These services will be bolstered with an FEE component provided via a youth development account described next.

In the FEE component, adolescents living with HIV will receive a youth development account with a 1:1 matched savings program at a financial institution accredited by the Bank of Uganda. Each youth development account will be opened in the adolescent’s name, with their primary caregiver as a cosigner, until the adolescent turns 18 years, at which time a cosigner will no longer be required. This is consistent with Ugandan banking law, which prohibits children aged <18 years from independently entering into a binding contract/operating a bank account. Family members and friends of adolescents living with HIV will be allowed and encouraged to contribute to this youth development account. It will be matched at a rate of 1:1 using money from the program. The match cap (maximum amount of youth contribution to be matched by the program) will be equivalent to US $20 per month or US $480 for the 24-month intervention period. During the intervention, adolescents will have direct access to both their personal savings deposited in the youth development account and the match provided by the study to pay for food, transportation to health clinics, and other necessities that may affect adherence. Matching will not be conditioned on the usual expenditure and/or savings goals dictated by programs [133,137,146]. The unconditional design recognizes that adolescents living with HIV and attending schools face competing demands (school fees, food for medication adherence, transport to clinics, etc) and that a conditional transfer may prohibit these vital expenditures, which may have implications for antiretroviral treatment adherence. In collaboration with participating financial institutions, the youth development account will be augmented with 4 sessions of financial literacy training, covering the basic principles of financial management, saving, and asset building.

#### Treatment Arm 2: MFG-HIVSR Plus FEE Plus GED-HIVSR

In addition to the bolstered usual care and MFG plus FEE described earlier, adolescents living with HIV in this arm will receive school-level HIV stigma reduction interventions targeting teachers, school nurses, matrons, and administrators (head teachers and director of studies) in their schools. The GED-HIVSR seeks to empower educators to reduce enacted HIV stigma and build supportive structures for adolescents living with HIV within their schools. Our rationale for adding this component to our intervention package is to test the added benefit of addressing school-level HIV stigma–related challenges on HIV treatment outcomes among adolescents living with HIV. Guided by an asset-based approach and drawing on evidence-based strategies for reducing HIV stigma in non–HIV-infected populations [63,97,98,147,148] and building support for adolescents living with HIV in school settings [149-151], GED-HIVSR seeks to impart educators in the intervention schools with HIV-related knowledge, provide a safe space for educators to explore their personal values and biases that may promote or hinder their role of supportive individuals and systems for adolescents living with HIV, and empower them with knowledge and skills to act as change agents within their schools.

The GED-HIVSR will be delivered as a 2-day workshop with a booster session in years 3 to 4. The details of each topic along with the targeted domain and delivery strategies are presented in Table 1. From each intervention school, we will recruit up to five educators including the school head teacher, director of studies, and school nurse. To standardize training and provide opportunities for peer-to-peer learning through group discussions, all educators will be convened at a central location for training. Workshop content will be delivered using a range of strategies including didactic lectures, role-play, testimonials from adolescents living with HIV, digital media (ie, documentaries), and discussions/brainstorming to promote participant engagement and active learning. Workshops will establish foundational knowledge on HIV transmission and treatment and cover content on HIV stigma and its impact on adolescents living with HIV and their families. Along with testimonials from adolescents living with HIV, we will use educational documentaries that portray the marginalization of people living with HIV to highlight the perpetuation of HIV stigma and its impact on these people, including adolescents living with HIV.

**Table 1 table1:** Topics, delivery strategies, and targeted domains of group-based HIV stigma reduction for educators.

Intervention topic			Intervention strategy		Targeted domain		Conceptual framework
HIV transmission, treatment, and prevention; misconceptions and misbeliefs about HIV; stereotypes about people living with HIV			Didactic lectures; role-play; discussions		HIV knowledge; feelings toward people living with HIV		Cognitive factors: knowledge and beliefs
HIV and AIDS stigma: understanding and defining manifestations of stigma; intersecting stigmas; consequences for adolescents living with HIV, their families and communities; awareness of HIV stigma in schools and communities; strategies for combating stigma			Educational; documentary; testimony from adolescents living with HIV		Stigma manifestations; intersecting stigma (eg, stigma and poverty); gender		Cognitive factors: knowledge and beliefs
Educators’ understanding of the needs and challenges of adolescents living with HIV in school settings, including barriers to HIV treatment adherence; mapping barriers to addressing HIV stigma within schools			Contact with adolescents living with HIV (presentations and testimonials from adolescents living with HIV)		Drivers and facilitators of stigma		Cognitive empathy; parasocial learning; skill building
Evaluating options for action planning for change; task analysis and developing an action plan; identification of stakeholders and resources to support initiatives to reduce stigma and support adolescents living with HIV in schools			Participatory learning through breakout sessions to brainstorm and develop actions plans for their schools		Future actions to support adolescents living with HIV; sustainable programs and policies to support adolescents living with HIV		Social learning theory: modeling; efficacy; empowerment through skill building
**Booster sessions**							
	Review of ongoing programs to support adolescents living with HIV in school setting (successes, challenges, and alternative strategies)	Empowerment; peer-to-peer learning		Institutionalizing change; knowledge generation and transfer		Social learning theory: modeling; efficacy; empowerment through skill building	

Previous studies have shown that direct or indirect contact (eg, digital film presentations) with stigmatized groups results in broader and more enduring reductions in stigma [152-154]. Thus, we will use expert testimonials from adolescents living with HIV as direct contact opportunities for the educators to hear their personal experiences in dealing with stigma and to *normalize* adolescents living with HIV as human beings; hence, fostering acceptance and empathy for adolescents living with HIV. Open discussions will provide a safe place for educators to express their views and opinions of adolescents living with HIV, as well as explore strategies, resources, and barriers to support adolescents living with HIV within schools. This strategy of actively engaging educators in examining their biases and developing supportive strategies for adolescents living with HIV within their settings is consistent with the principles of empowerment that build a sense of ownership. Participants will then act as change agents within their schools by implementing activities that address the needs of adolescents living with HIV. To facilitate context-specific discussions, we will conduct quarterly visits (at least one visit per academic term) to individual intervention schools in between the workshops to establish how educators are supporting adolescents living with HIV within their schools and offer additional services (eg, training) based on the requests from the schools.

### Ethics Approval and Consent

The research staff will obtain written informed consent and assent from the adult caregivers and children, respectively, before study enrollment. The consenting process for adults and children will be performed separately to avoid coercion. During face-to-face meetings, the adolescent’s primary caregiver will read and sign a standard consent form. In doing so, caregivers will be consenting to participation for themselves and assenting to the participation of their adolescents. Adolescents will sign an assent form that will be read aloud verbatim. If either the adolescent or caregiver refuses to participate, they will not be enrolled. According to the Uganda Law, emancipated minors, defined as persons aged ≤18 years who are pregnant, married, have a child, or are self-sufficient, will be allowed to consent on their own. Both consent and assent forms will be translated into Luganda (the most widely spoken local language in the study region) and back translated to English to ensure consistency. Both the assent and consent processes will be conducted verbally in Luganda, given that some caregivers and adolescents were illiterate. The study team will receive training on Good Clinical Practices so that sensitive research activities can be handled appropriately. In addition, all interviewers have completed the Collaborative Institutional Training Initiative certificate and National Institutes of Health certificate to safeguard the research participants.

We have obtained approval for the study procedures from the institutional review boards (IRBs) at the University of Washington in St. Louis, Missouri (IRB ID 202201128) and University of Michigan (HUM00211945) and from the in-country local IRBs in Uganda: Uganda Virus Research Institute (GC/127/867) and Uganda National Council of Science and Technology (SS1166ES).

The study has been registered with ClinicalTrials.gov (NCT05307250), as of April 1, 2022. The dissemination of the main study findings is targeted for 2025.

### Measures

As shown in Figure 1, assessment will be conducted at baseline and at 12-, 24-, and 36-month follow-ups. All assessments, each lasting approximately 60 minutes, will take place at the clinic during school breaks. Although all the adolescents living with HIV will be attending school and expect to be English-speaking (the instructional language in all Ugandan schools), assessments will be conducted in English or Luganda (the local language) depending on the English proficiency of the participants. All the interviewers will be fluent in English and Luganda. The questions will be translated from English to Luganda and back translated by a certified translator from a local university (Department of Languages) following standard procedures. The research team members who are fluent in Luganda and English will crosscheck all translated assessments. All the interviewers will receive highly structured and intensive training. Assessments will be conducted using standardized measures adapted from previous studies conducted in Uganda [104,133,141]. Any measures that have not been used will be pretested and made culturally appropriate to the Ugandan context. For questions measuring sensitive behaviors (eg, adherence), we will use audio computer-assisted self-interviews, where the participant takes the survey herself on a mini laptop. Nonsensitive questions will be administered by the interviewer. For the biological assay, blood specimens for HIV VL testing will be collected at baseline and 12, 24, and 36 months after the intervention. In accordance with the Abbott platform, VL will be dichotomized into undetectable (<40 copies/ml) and detectable (≥40 copies/ml) levels.

### Qualitative Component

Semistructured in-depth interviews will be conducted at baseline and at 12-, 24-, and 36-month follow-ups with adolescents living with HIV and their caregivers (n=40 dyads) in the 2 intervention arms. Baseline interviews will focus on the following aspects: (1) participants’ experience of decision-making (eg, costs, benefits, barriers, and facilitators) associated with HIV treatment adherence and (2) HIV stigma and its perceived impact on their lives. Follow-up interviews will unpack the longer-term impact, including experiences of stigma and key multilevel factors affecting HIV treatment–related behaviors of the participants after the intervention. Specifically, in addition to the baseline interview topics, 12-month interviews will examine the following: (1) experiences of the participants with their respective intervention components (ie, MFG-HIVSR, FEE, and GED-HIVSR), including perceived benefits and key multilevel (individual, family, school, contextual, and programmatic) influences that affect their participation and (2) intervention sustainability. In addition to topics explored at baseline (HIV stigma and decision-making on HIV treatment), the follow-up interviews will explore the sustained impact of the intervention to examine changes over time in HIV stigma and decision-making associated with treatment adherence and the sustained impact of the intervention over time.

In addition, educators (n=20) will be interviewed at baseline and at follow-up (12, 24, and 36 months). Baseline interviews will focus on their attitudes toward adolescents living with HIV and how HIV stigma manifests within their school context. Follow-up interviews, in addition to topics covered during baseline, will explore educators’ experiences with the training and resulting programs implemented within their school, facilitators and barriers to program implementation, recommendations, and sustainability. A purposive criterion sampling strategy [155] will be used to select adolescents living with HIV and their caregivers. adolescents living with HIV who score in the highest and lowest quartiles of internalized stigma at baseline (to be identified using the HIV stigma mechanism scale), and 20 participants (10 from each quartile) and their caregivers from each treatment condition will be randomly selected (n=40 dyads; these numbers will be sufficient for theoretical saturation) [156-158] and interviewed. This sampling method will ensure that participants with varying experiences are represented and will allow us to identify common patterns and variations across participants’ experiences. In addition, 20 educators across the 2 treatment arms will be randomly selected for interviews. Interviews will be conducted in English or Luganda, based on the participants’ preferences. The questions will be translated (English to Luganda) and back translated by research assistants, and then reviewed by 2 proficient team members ([name]). Each interview will last approximately 60 minutes and will be audiotaped. The same participants will be interviewed at each time point.

### Data Analysis

#### Primary Analyses for Aim 1

To examine the effect of M-Suubi on HIV viral suppression, we hypothesize the following:

H1a: MFG-HIVSR plus FEE will have higher odds of viral suppression than control participants (bolstered usual care).H1b: MFG-HIVSR plus FEE plus GED-HIVSR will have higher odds of viral suppression than control participants.H1c: MFG-HIVSR plus FEE plus GED-HIVSR will have higher odds of viral suppression than MFG-HIVSR plus FEE.

To test these 3 hypotheses, we will fit a 3-level generalized linear mixed model (LMM) with fixed effects for the study arm, time, and their interaction. Our analysis will follow an intent-to-treat approach, such that all participants are included in the analyses, irrespective of whether they have complete or incomplete outcome data. Maximum likelihood (ML) and multiple imputation (MI) procedures will be used to address missing data with sensitivity analyses. Sensitivity analyses will be performed using pattern-based MI to examine the robustness of the results under different missing data assumptions. We will use random intercepts for school/clinic ID to account for clustering of persons within schools and their affiliated clinics and include random intercepts, random slopes, and their covariance for person ID to account for clustering of repeated measurements within persons. Reflecting the binary HIV viral suppression outcome, a binomial distribution and log link will be used to fit a log-binomial model to estimate the relative risks. If the log-binomial model does not converge, we will substitute a Poisson model with robust SEs [159,160]. To maximize rigor, quasi-likelihood methods will not be used. Instead, maximum likelihood estimation via adaptive Gaussian quadrature with 15 integration points will be used to ensure stable solutions [161]. To test hypotheses H1a to H1c, we will perform 3 time-averaged comparisons of repeatedly measured observations across study arms to examine the intervention effects over the duration of the study period. As all possible comparisons among the 3 study arms will be evaluated, the α will be set at .05/3=.017 for each of these 3 planned comparisons. Any additional post hoc comparisons (eg, paired comparisons of groups at each time point) will maintain a nominal α of .05 using simulation-based step-down multiple comparison methods [114]. Our team has considerable experience fitting 3-level generalized LMMs to analyze data from our cluster randomized asset-based intervention trials [113,162].

#### Primary Analyses for Aim 2

To examine the effect of M-Suubi on HIV stigma, we hypothesize the following:

H2a: MFG-HIVSR plus FEE will have lower mean HIV stigma than control participants (bolstered usual care).H2b: MFG-HIVSR plus FEE plus GED-HIVSR will have lower mean HIV stigma than control participants.H2c: MFG-HIVSR plus FEE plus GED-HIVSR will have lower mean HIV stigma than MFG-HIVSR plus FEE.

To test these hypotheses, we will fit LMMs using the same fixed effects (study arm, time, and study arm-by-time) and random effects for the school/clinic (random intercepts) and person levels (random intercepts, random slopes, and their covariance) as proposed in the H1 analyses described earlier. To test hypotheses H2a to H2c, we will perform 3 time-averaged comparisons of repeatedly measured observations of stigma across study arms to examine the intervention effects over the duration of the study. To maintain a nominal type 1 error rate of 5% across tests of H2a to H2c, α will be set at .05/3=.017 for each planned time-averaged comparison. Our analyses will follow an intent-to-treat approach, and ML and MI approaches will be used to address missing data (as described in aim 1 earlier). To maximize rigor, the assumptions of normality and constant variance of residuals for these continuous outcomes in LMMs will be evaluated by examining histograms of the residuals and scatter plots of predicted values-by-Cholesky-scaled residuals, respectively. Transformations of outcomes will be used as needed to improve data conformance with model assumptions. Inferences for models whose residual statistics still do not fully meet assumptions following transformations will be generated via robust heteroskedastic-consistent Huber-White “sandwich” variance estimators [163]. All analyses will include outlier and influential case screening via the computation of Cook *D*, DF β values, and likelihood displacement statistics. If outliers are found, the results will be reported with and without outliers included [164,165].

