## Methods

### Study Overview

M-Suubi is a 5-year multilevel mixed methods randomized controlled trial. As shown in Figure 1, the M-Suubi intervention will be evaluated using a 3-arm cluster randomized trial implemented across 42 community health centers (with HIV clinics), targeting adolescents living with HIV aged 10 to 17 years and attending primary and secondary schools with a boarding section (n=14 clinics per arm; n=280 students per study arm). Adolescents living with HIV will be randomized at the clinic level to one of the three study conditions: (1) bolstered usual care, (2) MFG-HIVSR plus FEE, and (3) MFG-HIVSR plus FEE plus GED-HIVSR (Figure 1). M-Suubi will be provided for 20 months, with assessments at baseline and 12, 24, and 36 months.

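### The clinic, which is the randomized unit, has only a time-constant random effect, so if clinics drift apart over 36 months the time-specific arm comparisons get standard errors that are too small

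*Protocol article*

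**What the plan says.** Study Overview, on allocation: "Adolescents living with HIV will be randomized at the clinic level to one of the three study conditions", with "n=14 clinics per arm; n=280 students per study arm".

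Primary Analyses for Aim 1 specifies a three-level model with "fixed effects for the study arm, time, and their interaction". For the clinic level: "We will use random intercepts for school/clinic ID to account for clustering of persons within schools and their affiliated clinics". For the person level, the model will "include random intercepts, random slopes, and their covariance for person ID to account for clustering of repeated measurements within persons". Primary Analyses for Aim 2 carries the same structure to the stigma models: "random effects for the school/clinic (random intercepts) and person levels (random intercepts, random slopes, and their covariance".

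The confirmatory tests of H1a to H1c are averages over time: "we will perform 3 time-averaged comparisons of repeatedly measured observations across study arms", each at .05/3. H2a to H2c follow the same pattern. Further comparisons, for example "paired comparisons of groups at each time point", are labelled post hoc and are to hold a nominal .05 by a step-down method.

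Robust standard errors appear only as fallbacks: in Aim 1 if the log-binomial model fails to converge, in Aim 2 if residuals still misbehave after transformation. The level at which they would cluster is not given. The planned missing-data sensitivity analyses do not touch clinic trends.

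**The concern.** In a cluster-randomized trial each arm contrast should be judged against clinic-to-clinic variation in that same contrast. The stated model lets adolescents change at different rates but gives all clinics in an arm one common trend. Differing trends are plausible: the article itself notes that counselling varied before it was bolstered, and the interventions start after baseline.

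A shared clinic trend does not shrink as more adolescents are enrolled in that clinic. A model without a clinic-by-time term assigns it to persons and divides it by the clinic size. In any contrast of change the constant clinic intercept cancels, so arm-by-time is tested against person-level variation alone, as if adolescents had been randomized. Step-down adjustment corrects for multiplicity; it does not repair a standard error that is too small.

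This is not detail left to an analysis plan, because the article fixes the random effects at each level.

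**Working it through.** **Inputs from the article.** 14 clinics per arm; 840 × 0.85 = 714 participants, so 714/3 = 238 per arm and 238/14 = 17 per clinic; visits at 0, 1, 2 and 3 years; per-contrast level .05/3 = .0167. Sidedness is not stated; two-sided is assumed.

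**The article's own figure.** The minimum detectable effects of .26 to .35 cannot be reproduced uniquely, since no intraclass or within-person correlation is given. They are attainable: clinic correlation .01 to .02 with within-person correlation .3 to .5 gives .24 to .29, and clinic correlation .05 with within-person correlation .2 to .5 gives .33 to .35. They say nothing about clinic drift.

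**Assumed inputs (none in the article).** Person intercept variance .35, person slope variance .03 to .05, residual .45; clinic intercept variance .02; clinic slope variance .001 to .01 per year squared; no intercept-slope covariance; Gaussian outcome; t with 39 df.

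**Formulas.** For a contrast with visit weights a, the variance of a clinic mean is

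true V = .02(Σa)² + s(Σat)² + a′Wa/17,

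where s is the clinic slope variance and W the within-clinic covariance of one person's four visits. The factor 2/14 for an arm difference cancels in the ratio. The intercept-only model estimates one clinic variance, approximately .02 + s·t*², where t* = Σwt and w is proportional to W⁻¹1. Its variance for the contrast is that value times (Σa)², plus a′Wa/17. With r = √(model V / true V), actual error is P(|t39| > 2.50 r).

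**Worked case: s = .005, person slope variance .03.** The weights w are .362, .287, .213, .137, so t* = .287 + .426 + .411 = 1.12 years. The fitted clinic variance is .02 + .005 × 1.263 = .0263. In effect the model applies the clinic variance of about year 1.1 to every contrast.

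| Contrast | a′Wa/17 | True V | Model V | r | Actual error |
|---|---|---|---|---|---|
| Mean of 4 visits (centre 1.5 y) | (.35 + .0675 + .1125)/17 = .0312 | .0312 + .0312 = .0624 | .0263 + .0312 = .0575 | .96 | .021 |
| Mean of 3 post-baseline visits (centre 2 y) | (.35 + .12 + .15)/17 = .0365 | .0400 + .0365 = .0765 | .0263 + .0365 = .0628 | .91 | .029 |
| Month 36 (3 y) | (.35 + .27 + .45)/17 = .0629 | .0650 + .0629 = .1279 | .0263 + .0629 = .0892 | .84 | .043 |
| Linear arm-by-time | (.03 + .45/5)/17 = .0071 | .0050 + .0071 = .0121 | 0 + .0071 = .0071 | .77 | .063 |

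**Range.** A large-sample fit that also lets the person slope variance absorb part of the drift, over clinic slope variance .001 to .01 and person slope variance .03 to .05, gives at nominal .0167:

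- mean of four visits: .018 to .029
- mean of three post-baseline visits: .019 to .043
- month 36: .021 to .067

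**Cross-checks.**
- Simulation with 40,000 trials per scenario and clinic slope variance .005 to .01 gives .020 to .029, .027 to .042 and .039 to .063 for the same three contrasts. A clinic-time term brings the error back to .016 to .018. With no drift the planned model gives .012 to .015.
- A separate calculation on other inputs (total variance 1, clinic correlation .02 to .05, clinics holding 5 to 20% of a slope variance of .02 to .05) gives .0171 to .026 for four visits and .018 to .040 post-baseline. For arm-by-time the ratio of planned to correct standard error is .94 to .70, which is an error of .066 to .173 at nominal .05.

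**The case against.** The strongest reply is that the confirmatory tests are hardly touched. H1a to H1c and H2a to H2c are time-averaged, and the power statement counts four assessments. On that reading the standard error is short by only a few percent. This stands. A reader might infer that the primary tests are badly inflated; the documents do not support that. They leave open whether baseline belongs to the average, and only a post-baseline average would raise the figure materially.

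A reader might also want to headline change from baseline, where inflation is larger. The article states no such contrast, so it should not carry the point. Arm-by-time is in the model, but none of the six hypotheses tests it directly, and the visit-specific comparisons are labelled post hoc.

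The size is assumed, and the upper end is strong: at clinic slope variance .01 the clinic variance grows from .02 to .02 + .01 × 9 = .11 by month 36. If clinics hold the same share of slope variance as of intercept variance (.02/.37 = 5.4%), the four-visit test is at .018 to .020 and month 36 at .025 to .030. With no drift there is no inflation. The primary outcome is binary, and no calculation used the log-binomial model. These limits stand too.

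The robust-error fallbacks are not an answer: neither trigger detects clinic drift, and no clustering level is stated.

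**Conclusion.** The point holds as a conditional weakness in a stated modelling choice. If clinics differ in their trends, arm-by-time and visit-specific comparisons are judged against too small an error. At month 36 the actual error is about .021 to .067 against .0167. For the confirmatory tests the effect is slight with all four visits averaged and moderate with post-baseline visits only. The direction follows from the model structure. The size rests on the assumed clinic variances and the Gaussian approximation, so it should be read as an order of magnitude for Aim 2 and as indicative only for the binary Aim 1 outcome. It is worth correcting before analysis; it does not show that the primary tests are invalid.

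**What to change.** In Primary Analyses for Aim 1 and Aim 2, add a clinic-level random slope or a random clinic-by-visit effect, so that each arm contrast is tested against clinic variation in that contrast. State in advance what happens if the binary model will not fit it: either clinic-clustered robust standard errors with a small-sample correction for 14 clinics per arm, or a test on clinic-level summaries of the contrast. Apply this at least to every time-specific comparison. State also whether the time average includes baseline, since the exposure of the confirmatory tests depends on it.

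The cost is one or two extra variance parameters, some added convergence risk in a log-binomial model for which the article already plans a non-convergence fallback, and somewhat wider standard errors if drift is present. No extra data are needed.
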